### Procedure

In phase 1, following the initial eligibility screening and identification as possible participants, interested individuals will be contacted by emails or phone to invite them to schedule a 1-hour mock consent session with a member of the study team. Before the mock consent session, participants at UNC will e-sign an Web-based consent form sent by Qualtrics and those at MUSC provide verbal consent at the time of scheduling, which is confirmed by the coinvestigator prior to participating in study procedures. During the mock consent session, study personnel will give participants a brief overview of Doxy.me and teleconsent before walking participants through a mock consent form created for this study. The purpose of the mock consent form is not to actually complete an informed consent session but to highlight the functionalities of the software. Immediately after the completion of the mock consent process, study personnel will conduct audiorecorded, semistructured interviews with participants about their experiences. After the study completion, participants will either receive cash or a gift card sent electronically or mailed to their residence(s). In total, 40 participants are to complete phase 1 of the study at each site, for a total of 80 participants between UNC and MUSC.

For phase 2, participants (n=64 at each site) will be assigned to either consenting for the clinical trial through teleconsent (n=32) or through paper-based consenting (n=32). Notably, 64 subjects per site (totaling n=128 between sites) will provide 80% power to detect modest differences (effect sizes ~0.50) between groups with respect to the survey instrument scores. After consenting for participation in the teleconsent study, participants will undergo the informed consent process using either teleconsent or traditional consent. After the completion of the consent process, participants will immediately fill out the quality of informed consent (QuIC), Decision-Making Control Instrument (DMCI, and Short Assessment of Health Literacy-English version (SAHL-E). Thirty days postconsent, participants will be asked to fill out this set of surveys once more electronically; they will be paid for each set of surveys completed.

Study personnel who are consenting potential participants will fill out a NASA-TLX form for each patient; they will be paid for each form filled. In addition, they will fill out SUS 3 times throughout the study, once at the beginning of their participation, once toward the middle, and once after they have completed enrolling participants for the teleconsent study; they will be paid for each SUS filled out. Finally, after the termination of the teleconsent partnership, those who will be obtaining informed consent for these studies and will assist in the collection of instruments will be invited to participate in a focus group asking about their workload and perceptions of the Doxy.me software for teleconsent. Focus group participants will be receiving remuneration for completing the focus group.

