### Randomization

No randomization will be involved in phase 1. For phase 2, if the parent study permits, participants will be either randomly assigned to each of teleconsent or traditional consent. When random assignment is not possible, for example, in studies in which some participants do not have the option of being assigned to traditional consent, thereby negating random assignment, we will use the propensity score matching after assignment to either teleconsent or traditional consent. Once verbally consented through one of these means, participants will undergo the informed consent process.

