### Study Instruments

We will use the cognitive interviewing technique of verbal probing adapted from Willis to evaluate comprehension, decisions, and voluntariness, as proxies for users’ trust and intention to complete trials using the DMCI [22] and the QuIC [23] tool.

It is important to evaluate the decisional capacity and comprehension in informed consent processes, and research has identified that individuals with lower educational levels, mental illness, and advanced age are at risk of lower comprehension and potentially can be misled regarding the intent of the research [24]. To evaluate this, we will use the DMCI, a validated instrument that has been used to assess voluntary consent. The DMCI has a demonstrated internal consistency of 0.83 in psychometric studies [25]. The 9-item DMCI is used to assess perceived voluntariness, trust, and decision self-efficacy; in addition to a total score, it contains subscales addressing self-control, absence of control, and others’ control. In addition, the QuIC, a validated instrument that measures subjects’ understanding of the consent process in clinical trials and therapeutic misconception [23], is used to assess comprehension. The QuIC was designed to measure the actual (objective=20 items) and perceived (subjective=9 items) understanding of cancer clinical trials and can act as a screen for disclosure and capacity. The intraclass correlation coefficients (test-retest reliability) of.77 have demonstrated the reliability of this tool. We use the SAHL-E tool to measure health literacy. SAHL-E is an 18-item instrument that includes distractors on various health items, takes approximately 2 minutes to administer, and has a reliability of.89 [25].

In addition, validated surveys will be provided to all study personnel engaged in this process at the clinical trial sites to evaluate their level of satisfaction and workload experienced (NASA-TLX Task Index Scale) with the recruitment process [26,27]. NASA-TLX is a subjective workload assessment tool, which allows users to perform subjective workload assessments on operators working with various human-machine systems [26,27]. Using various metrics, including the QuIC tool [22], DMCI [23], SUS, the Doxy.me system through the NASA-TLX, SUS, and focus groups.

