### Data Analysis

In phase 1, all interviews will be professionally transcribed and imported into the NVivo 12.0 (QSR International Pty, Doncaster, VIC, Australia) qualitative analysis software. Verification of the transcript accuracy will be performed prior to analyzing the text. An iterative process will be used in the analysis of the data. Then, 2 team members will code the data following its transcription by tagging segments of text in the transcripts to a concept, expanding, refining, and reducing the concepts, and discussing the findings in detail to allow for cross-validation of findings between the 2 sites [28]. A coinvestigator at MUSC with advanced training in research ethics and bioethics will explore the ethical appropriateness and associated principles of teleconsent using an integrative bioethical approach, and the MUSC research team will review emerging findings at the midpoint and conclusion of coding to consider what additional data will be necessary to refine our understanding of the participants’ perspectives related to teleconsent and determine overall themes. In addition, any feedback about the Doxy.me software will be submitted to developers at MUSC.

In phase 2, for patient participants, descriptive statistics (means, SDs, medians, etc) of responses to the survey instruments will be used to characterize the 2 groups (ie, teleconsent vs paper-based consent). Participants will be stratified with respect to demographics and clinical study. Each of the survey instrument summary scores and subscale scores will be essentially continuous variables; as such, comparisons between groups will be delineated through analysis of covariance modeling. In these models, the instrument score will serve as the dependent variable, with the experimental group serving as the key independent variable of interest. The analysis of covariance model includes participant factors, such as education and other demographics, as covariates in the models.

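### Health literacy (SAHL-E) is measured only after the consent session, repeated at 30 days and, as the analysis is worded, compared between arms as an outcome, while its use as a covariate is not stated

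*Protocol article*

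**What the plan says.** **Timing (Procedure).** After the phase 2 consent process, "participants will immediately fill out the quality of informed consent (QuIC), Decision-Making Control Instrument (DMCI, and Short Assessment of Health Literacy-English version (SAHL-E"). Then: "Thirty days postconsent, participants will be asked to fill out this set of surveys once more electronically". No earlier administration is described, and the Screening section says phase 2 has no participant screening.

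**Analysis role (Data Analysis).** "Each of the survey instrument summary scores and subscale scores will be essentially continuous variables", and in the ANCOVA models "the instrument score will serve as the dependent variable, with the experimental group serving as the key independent variable of interest". On adjustment: "The analysis of covariance model includes participant factors, such as education and other demographics, as covariates in the models". SAHL-E is neither exempted from the first rule nor named under the last.

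**Purpose (Study Instruments).** QuIC is given as the measure of comprehension, and DMCI as the measure of perceived voluntariness, trust and decision self-efficacy. For the third instrument the article says only: "We use the SAHL-E tool to measure health literacy". It has 18 items, takes about 2 minutes and has a reported reliability of .89.

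**Assignment (Randomization).** Where a parent study does not allow random assignment, "we will use the propensity score matching after assignment to either teleconsent or traditional consent".

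**Hypothesis (Discussion).** The hypothesis concerns quality of informed consent and staff workload. Health literacy is not part of it.

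**The concern.** Nothing in the article suggests that the mode of a single consent session should alter a person's health literacy. A between-arm test of SAHL-E therefore has no treatment effect to estimate. A difference could come from chance imbalance, from who ends up in each arm in the non-randomized parent studies, or from how the form was given (Data Management allows web surveys or pen and paper). A reader could mistake any of these for an effect of teleconsent.

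The same score is also a natural predictor of comprehension. The Study Instruments section itself says that people with lower education are at risk of lower comprehension. Without a stated covariate role for SAHL-E, the QuIC comparison may lose precision that the study has already paid to collect.

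Timing adds a smaller difficulty. A score first taken after the assigned session is not a clean pre-assignment variable for propensity matching, and anyone who stops before the surveys has no value.

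**Working it through.** **1. Role of SAHL-E as written.** Procedure puts three instruments in the survey set. Data Analysis applies the dependent-variable rule to each instrument score. SAHL-E is in the set and not exempted, so on the plain wording it is compared between arms at both times. Counting scores from Study Instruments:

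- QuIC: objective and subjective, 2
- DMCI: total and three subscales, 4
- SAHL-E: 1

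That is 7 scores × 2 times = 14 between-arm comparisons, of which 2 are SAHL-E.

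**2. The stated power.** Inputs from Procedure: "64 subjects per site (totaling n=128 between sites"), hence 64 per arm when the sites are pooled; effect size about 0.50; power 80%. The two-sided alpha of .05 is stated in the study-personnel paragraph and is assumed to apply here too.

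Normal approximation: power = Φ(d × √(n/2) − 1.96) = Φ(0.50 × √32 − 1.96) = Φ(2.828 − 1.96) = Φ(0.868) = 80.7%. The noncentral t gives 80.1%. The stated 80% reproduces for the pooled sample. (At 32 per arm, one site alone, it would be about 50%; that is a separate matter.)

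**3. Effect of adding SAHL-E as a covariate.** Let r be the correlation of SAHL-E with QuIC after the demographic covariates. The article gives no value, so r is an assumption. The 0.50 is taken relative to the SD before SAHL-E is added. The residual SD is then multiplied by √(1 − r²), the standardized difference becomes 0.50/√(1 − r²), and the equivalent sample-size ratio is 1/(1 − r²).

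| assumed r | √(1 − r²) | power, normal | power, t | n per arm for 80% (normal) | sample-size ratio |
|---|---|---|---|---|---|
| 0 | 1.000 | 80.7% | 80.1% | 63 | 1.00 |
| 0.2 | 0.980 | 82.3% | 81.7% | 61 | 1.04 |
| 0.3 | 0.954 | 84.3% | 83.7% | 58 | 1.10 |
| 0.4 | 0.917 | 87.0% | 86.5% | 53 | 1.19 |
| 0.5 | 0.866 | 90.4% | 90.0% | 48 | 1.33 |

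Example at r = 0.3: 2.828/0.954 = 2.965; 2.965 − 1.96 = 1.005; Φ(1.005) = 84.3%.

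Education is already named as a covariate and probably overlaps with literacy, so the lower rows should be taken as seriously as the upper ones.

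**The case against.** The strongest reply is that the article never names SAHL-E as an outcome. The dependent-variable rule is one generic sentence covering three instruments; elsewhere SAHL-E is described only as a measure of literacy, and the hypothesis leaves it out. This stands as far as intention goes: the authors may never have meant to test it. The sentence as written nevertheless includes it, and the 30-day repeat gives it the schedule of an outcome.

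A reader might infer that the plan excludes health literacy from adjustment. The documents do not support that. The covariate list is introduced by way of example and is open, and a full list may sit in an analysis plan that is not shown. The supported point is narrower: the role is not stated, and if SAHL-E were both outcome and covariate the text would give one variable two conflicting roles.

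A reader might also infer that a key confounder is left out of the propensity score. The Randomization section lists no propensity variables at all, so no omission is shown. Only the post-session timing can be criticized there.

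There is also a fair point about consistency. If literacy is stable, a score taken just after the session is close to a baseline score and could be used for adjustment without being moved. That is accepted. What remains against it is the possible influence of survey mode and of missing values, neither of which can be sized from the article.

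Finally, earlier administration has drawbacks. It adds a step before consent in the partner trials, a literacy test just beforehand might affect attention or DMCI self-efficacy answers, and concealing the mode is impossible where a participant has no paper option.

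**Conclusion.** The point holds in a limited form. As worded, the plan compares SAHL-E between arms at two times, though no effect of consent mode on it is expected, and does not state its more useful role as a predictor of QuIC. The outcome role and the 30-day repeat are the clearer faults; the timing of the first measurement is secondary.

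The gain from adjustment is about 2 points of power at r = 0.2 and about 10 points at r = 0.5. It rests on an assumed correlation and on pooling both sites. The stated 80% does not depend on this covariate and is not wrong on this account. That health literacy is stable over one session is a methodological judgement; it fits the article's description of the instrument but is not stated there. This is a worthwhile, inexpensive improvement, not a flaw on which the main conclusions depend.

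**What to change.** - **Data Analysis:** limit the dependent variables to QuIC and DMCI scores, and report SAHL-E descriptively by arm as a participant characteristic. Name it as a covariate in the QuIC and DMCI ANCOVAs.
- **Randomization:** name SAHL-E as a candidate variable for the propensity score in parent studies without random assignment.
- **Procedure:** give SAHL-E once, in the same format in both arms, after consent to the teleconsent study and before the parent-study consent session, and before the mode is revealed where feasible. Remove it from the 30-day set.
- **Fallback:** if it cannot be moved, use the immediate post-session score as an approximate covariate and say so.

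**Cost:** a 2-minute form moves ahead of the consent session in the partner trials' workflow, and one repeat is deleted. The rest is wording. The sample size and its justification are unchanged.

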### Study Instruments

We will use the cognitive interviewing technique of verbal probing adapted from Willis to evaluate comprehension, decisions, and voluntariness, as proxies for users’ trust and intention to complete trials using the DMCI [22] and the QuIC [23] tool.

It is important to evaluate the decisional capacity and comprehension in informed consent processes, and research has identified that individuals with lower educational levels, mental illness, and advanced age are at risk of lower comprehension and potentially can be misled regarding the intent of the research [24]. To evaluate this, we will use the DMCI, a validated instrument that has been used to assess voluntary consent. The DMCI has a demonstrated internal consistency of 0.83 in psychometric studies [25]. The 9-item DMCI is used to assess perceived voluntariness, trust, and decision self-efficacy; in addition to a total score, it contains subscales addressing self-control, absence of control, and others’ control. In addition, the QuIC, a validated instrument that measures subjects’ understanding of the consent process in clinical trials and therapeutic misconception [23], is used to assess comprehension. The QuIC was designed to measure the actual (objective=20 items) and perceived (subjective=9 items) understanding of cancer clinical trials and can act as a screen for disclosure and capacity. The intraclass correlation coefficients (test-retest reliability) of.77 have demonstrated the reliability of this tool. We use the SAHL-E tool to measure health literacy. SAHL-E is an 18-item instrument that includes distractors on various health items, takes approximately 2 minutes to administer, and has a reliability of.89 [25].

In addition, validated surveys will be provided to all study personnel engaged in this process at the clinical trial sites to evaluate their level of satisfaction and workload experienced (NASA-TLX Task Index Scale) with the recruitment process [26,27]. NASA-TLX is a subjective workload assessment tool, which allows users to perform subjective workload assessments on operators working with various human-machine systems [26,27]. Using various metrics, including the QuIC tool [22], DMCI [23], SUS, the Doxy.me system through the NASA-TLX, SUS, and focus groups.

### Study Design

The design of phase 1 of our study is a qualitative study with a semistructured interview format. The ethical approval was obtained from the Institutional Review Boards at the UNC (17-2769) and the MUSC (# Pro00068715).

The design of phase 2 of our study is a 2-arm, teleconsent study, which assesses various metrics using standardized surveys. The ethical approval was obtained from the Institutional Review Board at the UNC (17-2870).

### Data Management

Survey assessments and demographics will be collected through UNC Qualtrics survey, REDCap survey, or pen-and-paper. Interview audios will be recorded using a handheld device (following participants’ consent) and stored on a secure MUSC Box server.

### Data Analysis

In phase 1, all interviews will be professionally transcribed and imported into the NVivo 12.0 (QSR International Pty, Doncaster, VIC, Australia) qualitative analysis software. Verification of the transcript accuracy will be performed prior to analyzing the text. An iterative process will be used in the analysis of the data. Then, 2 team members will code the data following its transcription by tagging segments of text in the transcripts to a concept, expanding, refining, and reducing the concepts, and discussing the findings in detail to allow for cross-validation of findings between the 2 sites [28]. A coinvestigator at MUSC with advanced training in research ethics and bioethics will explore the ethical appropriateness and associated principles of teleconsent using an integrative bioethical approach, and the MUSC research team will review emerging findings at the midpoint and conclusion of coding to consider what additional data will be necessary to refine our understanding of the participants’ perspectives related to teleconsent and determine overall themes. In addition, any feedback about the Doxy.me software will be submitted to developers at MUSC.

In phase 2, for patient participants, descriptive statistics (means, SDs, medians, etc) of responses to the survey instruments will be used to characterize the 2 groups (ie, teleconsent vs paper-based consent). Participants will be stratified with respect to demographics and clinical study. Each of the survey instrument summary scores and subscale scores will be essentially continuous variables; as such, comparisons between groups will be delineated through analysis of covariance modeling. In these models, the instrument score will serve as the dependent variable, with the experimental group serving as the key independent variable of interest. The analysis of covariance model includes participant factors, such as education and other demographics, as covariates in the models.

For study personnel, descriptive statistics will be used to study the differences in the NASA-TLX between the 2 groups through a 2-sample *t* test of means. The sample size of the research assistant group will be based on the number of research assistants currently working on the clinical trials. Regardless, we will assume 2-sided hypothesis testing with an alpha level of.05. We suspect that the null hypothesis will display no significant difference in the means of the research assistants’ NASA-TLX scores for teleconsent versus paper-based consenting.

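### Phase 2 compares 12 to 14 patient scores between arms with no primary score or time point, while the 80% power is correct only for one such comparison

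*Protocol article*

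**What the plan says.** All places are in the protocol article.

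- **Analysis rule (Data Analysis, phase 2 patients).** "Each of the survey instrument summary scores and subscale scores will be essentially continuous variables; as such, comparisons between groups will be delineated through" ANCOVA, with arm as the independent variable of interest. No score is ranked above another.
- **Scores (Study Instruments).** QuIC has an objective and a subjective part. For DMCI, "in addition to a total score, it contains subscales addressing self-control, absence of control" and others' control. SAHL-E gives one health-literacy score.
- **Timing (Procedure).** The three instruments are completed straight after the consent process. Then, "Thirty days postconsent, participants will be asked to fill out this set of surveys once more electronically". The Discussion says that both administrations serve to find differences in understanding between the groups.
- **Power (Procedure).** "64 subjects per site (totaling n=128 between sites) will provide 80% power to detect modest differences (effect sizes ~0.50) between groups", with the endpoint given only as a difference "between groups with respect to the survey instrument scores".
- **Significance level (Data Analysis).** "Regardless, we will assume 2-sided hypothesis testing with an alpha level of.05". This sentence stands in the study-personnel paragraph, which concerns NASA-TLX.
- **Hypothesis (Discussion).** No significant difference between teleconsent and paper in the quality of informed consent.

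**The concern.** The Discussion promises one verdict on the quality of consent, but the analysis rule produces a dozen or more arm comparisons and does not say which of them decides. With mixed results, one nominally significant subscale could be taken as refuting the hypothesis. Equally, a real difference in objective understanding could be outweighed by several null DMCI subscales. Either reading could be chosen after the data are seen.

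The sample-size statement has the same gap. It assures 80% power for the survey scores as a group, which a reader may take as a property of the whole set of comparisons. The authors hope that the results will increase use of teleconsent, so the basis for the conclusion should be fixed beforehand.

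**Working it through.** **1. Reproduce the stated power.** Inputs from Procedure: standardized effect d = 0.50 and N = 128. Allocation is 32 versus 32 at each site, hence 64 versus 64 pooled. Two-sided α = .05 is assumed here, because the paragraph on patient scores gives no level.

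- Noncentrality: d·√(n/2) = 0.50 × √32 = 2.828.
- Normal approximation: Φ(2.828 − 1.960) = Φ(0.868) = 0.807. Exact noncentral t: 0.801.
- Alternatives that do not fit: one-sided .05 gives 0.88; a single site (32 versus 32) gives 0.50 to 0.52.

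The 80% is therefore right for one unadjusted two-sided .05 comparison on the pooled sample. The match is also the basis for inferring .05 for the patient scores.

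**2. Count the comparisons.**

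- QuIC: 2 (objective, subjective).
- DMCI: 4 (total and three subscales).
- SAHL-E: 1, if the rule is read literally.

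Two time points give (2 + 4) × 2 = 12 without SAHL-E and (2 + 4 + 1) × 2 = 14 with it.

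**3. Chance of at least one spurious arm difference if all are tested unadjusted at .05.**

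- Independent tests: 1 − 0.95^k. For k = 12: 1 − 0.540 = 0.460. For k = 14: 1 − 0.488 = 0.512.
- Correlated tests: multivariate normal test statistics. The article gives no correlations between scores, so these are assumptions.

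| Common correlation | 12 tests | 14 tests |
|---|---|---|
| 0 | 46% | 51% |
| 0.3 | 40% | 44% |
| 0.5 | 32% | 35% |
| 0.7 | 23% | 25% |

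A more structured check takes the DMCI total as the sum of its subscales and uses the article's QuIC test-retest value, .77, as a stand-in for the correlation between the two times. With correlations of 0.3 to 0.5 within an instrument and 0 to 0.3 between instruments, the result is 30 to 36% for 12 tests and 35 to 41% for 14. With 0.7 within, 0.3 between and 0.8 over time, it is 26.5% and 31.5%.

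**4. Power if the whole family were controlled.** Bonferroni over 14 gives α = .05/14 = .0036, critical value 2.914.

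- Normal approximation: Φ(2.828 − 2.914) = Φ(−0.086) = 0.466. Exact t: 0.447.
- Patients needed for 80% power: 113 per arm (normal approximation), against the planned 64.

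**The case against.** The strongest defence has four parts.

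- **An adjustment may exist elsewhere.** The article does not say that the tests are unadjusted, and multiplicity rules often sit in an analysis plan, which is not shown here. This stands: a missing adjustment is not the point, and the error rates above are conditional. It does not answer the missing primary, which belongs in the protocol beside the sample size it justifies. A later adjustment over all scores would also pull power below the stated 80%.
- **The power sentence is not false.** The effect is standardized, so 80% is correct for any one score taken singly. This stands: the statement is unspecific, not miscalculated.
- **The text leans towards QuIC.** The aims speak of perception and comprehension, Study Instruments assigns comprehension to QuIC, and the Discussion speaks of understanding. This narrows the field, but it does not choose between the objective and subjective parts or between the two times.
- **Fourteen independent tests is an upper bound.** SAHL-E may be meant as a participant characteristic, DMCI total and subscales share the same nine items, and the 30-day scores repeat the first ones on the same people. This stands, and it is why a range is given.

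Two stronger readings are tempting. A reader might infer that the false-positive risk is definitely 35 to 50%; that holds only for 14 unadjusted tests with correlations of about 0.5 or less. A reader might also infer that each time point is modelled separately, so that the 30-day results rest on completers alone. The article does not say how the two times are modelled or how missing 30-day forms are handled, so it does not support that claim.

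**Conclusion.** The point holds in a limited form. Phase 2 plans 12 to 14 arm comparisons with no primary score or time point, and its 80% power describes one unadjusted comparison without saying which. Neither statement depends on an assumed correlation.

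The size of the false-positive risk does. It is roughly 23 to 51%, against a nominal 5%, and it rests on three assumptions: no adjustment, a .05 level for patient scores, and common correlations between 0 and 0.7, with SAHL-E either in or out. Even the lowest figure is more than four times the nominal level. This should be corrected before phase 2 data are analysed, but it does not undermine the design.

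**What to change.** - Name one primary score and one time point in the protocol. QuIC objective understanding immediately after consent is an example that fits the comprehension aim; the choice is the investigators'.
- Attach the 80% power statement to that comparison, and state its two-sided .05 level in the paragraph on patient scores.
- Base the conclusion on the consent-quality hypothesis on that comparison, reported with its 95% CI.
- Report QuIC subjective understanding, all DMCI scores and all 30-day results as supportive estimates with 95% CIs. State whether SAHL-E is an outcome or a participant characteristic.
- Do not add a DMCI test that is conditional on success of the primary. Success has no clear meaning when the stated hypothesis is no significant difference.

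With one designated comparison, the type I error is 5% and power at d = 0.50 stays at 80 to 81% with 64 per arm. The cost is protocol wording, with no extra patients or data. The downside is that subscale and 30-day findings become supportive only.
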